### Treatment Phase (Phase B)

All participants will receive an outpatient interdisciplinary rehabilitation treatment in secondary care. This treatment aims to increase patients’ levels of activity, participation in daily life, and HRQoL regardless of the level of complaints they experience. During phase B, participants are invited to fill in a daily diary for 40 days (Figure 1).

The treatment team consists of a rehabilitation physician, physiotherapist, occupational therapist, speech therapist, and psychologist. The team is experienced in interdisciplinary rehabilitation treatment with a biopsychosocial approach. Education has been given and supervision team meetings are planned monthly. For each participant, the content of the interdisciplinary rehabilitation treatment will be personalized according to the participant’s individual physical, mental, and cognitive complaints and personal goals. As a result, input from the various disciplines can vary according to the participant’s problem profile and needs. The individual goals are activity- and participation-oriented and determined during the intake with the rehabilitation physician and further specified during the treatment (eg, “being able to vacuum the entire house”). The Canadian Occupational Performance Measure (COPM), administered by an occupational therapist, will be used to support individual goal setting. The COPM was developed to set treatment goals based on problems experienced by the patient in daily activities [25,26]. The rehabilitation physician is the team supervisor and has final medical responsibility for the participants during the study period.

The interdisciplinary rehabilitation treatment lasts 12 weeks, with the patient receiving therapy approximately 3 half days per week (depending on their goals and initial capacity). In order to improve the level of functioning, the first 4 weeks consist of an assessment phase, in which the various disciplines gain insight into the participant’s complaints, functional capabilities, and the potential to strengthen physical and mental resilience. After this first phase, a multidisciplinary consultation (MDC) takes place with all disciplines involved. During this MDC, an individual model explaining the level of COVID-19–related disability is proposed, based on the interaction of the disabling factors involved. The team will propose an 8-week treatment plan tailored to the patient’s individual problems and goals. After this MDC, the patient will receive an interdisciplinary education from the treatment team in which the proposed individual explanatory model from a biopsychosocial perspective is discussed with the participant, including the hypothesized disabling factors that interfere with performing activities and participation in daily life. This education with a biopsychosocial approach is aimed at increasing mental and physical resilience despite the PCC complaints. Another MDC will take place in weeks 7 and 11 to discuss the progress in the treatment process and whether treatment goals or treatment plans should be adjusted. After each MDC, the rehabilitation physician provides all feedback to the participant and discusses the proposed plan according to principles of shared decision-making. If necessary, the rehabilitation physician will give additional biopsychosocial education. There will be a follow-up consultation with the rehabilitation physician after 3 months of completing the treatment phase.

The following are the commitment of disciplines within the interdisciplinary rehabilitation treatment and the contribution of the disciplines can vary according to the patient’s profile and needs.

Rehabilitation physician, at least 4 times (45 minutes for the first consultation, 15 minutes for a regular consultation): first consultation, after the MDC, and follow-up consultations.Physiotherapy, 2 times per week (each session takes 60 minutes), for improving physical performance such as physical condition and muscle strength through functional training and hydrotherapy and to guide in case of any pain- or tension-related complaints [11,27]. Patients are also encouraged to experience movement possibilities and will be encouraged to be as active as possible, regardless of the number and severity of complaints, particularly for valuable activities and social participation.Occupational therapy, 2 times per week (each session takes 60 minutes), for education in energy management and recognizing and pushing boundaries. The occupational therapist helps in resuming and building up daily activities (such as household duties, leisure activities, or work) despite the level of complaints [11,28].Speech therapy, 2 times per week (each session takes 30 minutes), for breathing exercises in case of dyspnea complaints, dysfunctional breathing, or dysfunction of the diaphragm [11].Psychotherapy, once a week (each session takes 60 minutes). To strengthen a person’s resilience, first and second-generation CBT as well as third-generation CBT (ACT) will be applied. CBT aims to improve quality of life by strengthening individual resilience to cope with complaints [19,29]. The treatment can include a variety of techniques such as psychoeducation, verbal challenge techniques (learning to critically examine dysfunctional thoughts), behavioral experiments, skills training, breathing and relaxation exercises, stress management, problem-solving skills, and exercises to broaden sensory perception. The goal of ACT is growth in psychological flexibility [18]. The emphasis here is not on controlling and changing, but on accepting thoughts, behavior, feelings, and experiences such as negative physical experiences, fatigue, and pain.

### Follow-Up Phase

The follow-up phase takes 12 weeks and starts directly after phase B. In the last 2 weeks of the follow-up phase, participants are invited to fill in a daily diary. The number of days (7,8, 9, or 10) a participant must fill in a daily diary during the last 2 weeks of the follow-up phase, will be randomized by a dedicated computer program (YourResearch). Phase B will start directly after phase A.

### Assessment

Since PCC can affect different domains of functioning, measurements were chosen based on an integral vision of health and include body function impairments, activity limitations, and participation restrictions as well as personal factors, according to the *International Classification of Functioning, Disability and Health* [7]. All variables will be measured by daily diary items, validated questionnaires, and physical examination (Figure 1 and Tables 1-3). Based on design standards, the recommended minimum number of baseline measurements in an R-SCED study is 5 [30]. In this study, daily diaries will be completed for 7 to 10 days (baseline measurements) in phase A. In addition, there are 40 measurements during the rehabilitation treatment and a minimum of 7 to 10 follow-up measurements. The validated self-administered questionnaires will be collected at the start of phase A (T0), at the end of phase B (T1), and after 3 months of follow-up (T2). Participants will complete the questionnaires and the daily measurements with an app (YourResearch) on a computer or mobile device.

**Table 1 table1:** Overview of the secondary outcome measurements: body function.

Secondary outcome measurements	Measurement instrument	T0^a^	T1^b^	T2^c^
Muscle strength	Muscle strength is a commonly used test for physical function [31]. A Jamar HHD^d^ is used for handgrip muscle strength [32,33]. Muscle strength of the knee extensor or flexor is measured using a dynamometer (Biodex System 3 Pro Dynamometer) [34].	✓	✓	
Fatigue	MFIS^e^: this is a 21-item metric for fatigue severity. A total score is calculated as the sum of the subscale scores (0-84). Higher scores indicate higher levels of fatigue [35].	✓	✓	✓
Breathlessness	MRC^f^ breathlessness scale: ranging from 1=no trouble with breathlessness to 5=I am too breathless to leave the house [36].	✓	✓	✓
Pain	NRS^g^: mean pain intensities in the last 7 days, ranging from 0 to 10 [37].	✓	✓	✓
Cognitive function	CFQ^h^: this is a 25-item self-report questionnaire. The total scores range from 0 to 100, with higher scores reflecting a report of more frequent cognitive errors in everyday life [38,39].	✓	✓	✓

^a^T0: beginning of baseline phase (phase A).

^b^T1: after completion of the treatment phase (phase B).

^c^T2: after completion of the follow-up phase.

^d^HHD: handheld dynamometer.

^e^MFIS: Modified Fatigue Impact Scale.

^f^MRC: Medical Research Council.

^g^NRS: Numerical Rating Scale.

^h^CFQ: Cognitive Failure Questionnaire.

### Outcome Measurement

#### Primary Outcome Variables

The primary outcome measurements are participation in society and HRQoL. A daily diary will be used, including a short (10-item) questionnaire to assess changes over time. The daily diaries consist of 8 questions selected from the validated questionnaires: Utrecht Scale for Evaluation of Rehabilitation-Participation (USER-P), EQ-5D-5L, and the Hospital Anxiety and Depression Scale (Multimedia Appendix 1). Each question is rated on a scale from 0 to 10. In addition, the daily dairy will focus on 2 most important individual goals (the participant will be asked to rate each goal on performance and satisfaction, on a scale from 0 to 10, based on the COPM score). The individual goals are determined by the patient, immediately after inclusion in the study.

Validated self-administered questionnaires will also be used. Participation in society will be assessed by USER-P. The USER-P consists of 3 subscales: the frequency of activities, the restriction subscale, and the satisfaction subscale. For all 3 subscales, the total score ranges from 0 to 100, with higher scores indicating better participation [40,41]. HRQoL is evaluated with the 5-dimension descriptive system (EQ-5D-5L) and the associated visual analog scale [42]. The EQ-5D-5L includes 5 domains, namely, mobility, self-care, usual activities, pain, and anxiety or depression. Each dimension is rated on a 5-level scale from “no problems” to “unable.” For the resulting 5-digit EQ-5D health profile, a weighted EQ index was calculated using Dutch reference values [43]. The EQ-5D-5L visual analog scale asks the participant to value their perceived health from 0=the worst imaginable health to 100=the best imaginable health, with higher scores indicating higher quality of life.

#### Secondary Outcome Variables

Secondary outcome variables are presented in Tables 1-3. Body function impairments (muscle strength, fatigue, breathlessness, pain, cognitive impairments), activity limitations (functional exercise, perceived limitations in daily life), participation (individual goals, activity and participation oriented), and personal factors (baseline characteristics, anxiety, depression, coping style and resilience) are assessed combined with physical examination and validated self-administered questionnaires. Details of the measurement instruments are also presented in Tables 1-3.

**Table 2 table2:** Overview of the secondary outcome measurements: activity limitations and participation.

Secondary outcome measurements	Measurement instrument	T0^a^	T1^b^	T2^c^
Functional exercise	6MWT^d^: a submaximal exercise capacity by walking distance. The distance reached will be recorded in meters [44]. STS^e^: for functional mobility, balance, and lower limb strength. Time in seconds is the main outcome [45,46]. The 2-minute SCT^f^: a submaximal exercise capacity. The number of steps is the main outcome [47]. The 6MWT, STS, and SCT will be performed by an experienced physiotherapist.	✓	✓	
Perceived limitations in daily life	PROMIS^g^ physical function short form 8b: has 8 questions. Higher scores indicate better physical function [48,49]	✓	✓	✓
Individual goals, activity, and participation oriented	COPM^h^: to set treatment goals based on problems experienced by the patient in daily activities and will be administered by an occupational therapist [25,26].	✓	✓	

^a^T0: beginning of baseline phase (A).

^b^T1: after completion of the treatment phase (B).

^c^T2: after completion of the follow-up phase.

^d^6MWT: 6-minute walk test.

^e^STS: Sit-to-stand test.

^f^SCT: stair climbing test.

^g^PROMIS: patient-reported outcomes measurement information system.

^h^COPM: Canadian Occupational Performance Measure.

**Table 3 table3:** Overview of the secondary outcome measurements: personal factors.

Secondary outcome measurements	Measurement instrument	T0^a^	T1^b^	T2^c^
Baseline characteristics	Age, sex, weight, education level, and marital status, as well as information about the time of COVID-19 infection, current complaints since the COVID-19 infection, the need for hospitalization due to COVID-19 infection, who diagnosed the post–COVID-19 condition, and previous treatments for the post–COVID-19 condition (open question and participant opinion).	✓		
Anxiety and depression	HADS^d^: this is a 14-item self-rated scale. The total score ranges from 0 to 21. A score ≥8 on either subscale is considered to be substantial anxiety or depression symptoms [50].	✓	✓	✓
Proactive coping skills	UPCC^e^: a 21-item self-assessment tool. The total score was the average for all item scores (range 1-4), higher scores indicate higher levels of proactive coping [51].	✓		
Resilience	BRS^f^: a 6-item questionnaire. The total score is the mean score of all answers (range 1-5). Higher scores indicate a better-developed ability of resilience [52,53]	✓		

^a^T0: beginning of baseline phase (phase A).

^b^T1: after completion of the treatment phase (phase B).

^c^T2: after completion of the follow-up phase.

^d^HADS: Hospital Anxiety and Depression Scale.

^e^UPCC: Utrecht Proactive Coping Scale.

^f^BRS: Brief Resilience Scale.

### Sample Size Calculation

Experience from previous single-case experimental design (SCED) studies showed that the sample size varies between 6 and 27 participants [54-56]. One of our earlier prospective cohort studies was used in calculating the sample size. In this study, the USER-P was the primary outcome and improved in the first year after ICU discharge, [8]. In this cohort, the effect size based on changes in the level of participation appeared to be medium from baseline to 12 months follow-up (>0.5), with a statistical power of >0.8. Using the calculation tool developed by Bouwmeester and Jongerling [57] for SCED studies, with a medium effect size, the number of measurements, and accounting for loss-to-follow-up, 20 patients need to be included in this study. Patients withdrawn from the study will not be replaced. All analysis will be performed according to the “intention-to-treat” principle.

### Statistical Analysis

Baseline and demographic characteristics will be presented in means (SD), medians (IQR), or percentages, as appropriate.

For our primary outcome measurements, the daily dairies, the statistical analysis will be performed using the Shiny app (KU Leuven) for single-case data analysis [58]. The following steps will be taken to test the effects of the intervention. First, in visual analysis, the within-case data of the daily dairies will be plotted and visually inspected per participant with respect to within-phase (eg, level, trend, variability) and between-phase characteristics (eg, immediacy of effect, overlap, consistency) [59]. Second, the percentage of nonoverlapping pairs between phases will be used to calculate the effect size of each participant. Nonoverlapping data between phases indicate performance differences between phases and is an important part of visual analysis in single-case research [60]. The Nonoverlap of All Pairs is an index of data overlap between phases in single-case research [60]. The Nonoverlap of All Pairs equals the number of comparison pairs showing no overlap, divided by the total number of comparisons. It can be calculated as an area under the curve [60]. Third, randomization tests will be performed to test the null hypothesis; that the interdisciplinary rehabilitation treatment has no effect on participation levels and HRQoL. The observations of the baseline phase will be compared to those of the intervention and follow-up phases, respectively (*mean phase A – mean phase BC = test statistic*, where C is the follow-up phase). Because the starting point of phase B (intervention) is randomly determined and the follow-up phase does not include any new intervention methods, phase B and the follow-up phase are combined. In case visual analysis suggests delayed effects, the randomization test will be repeated with lagged data until the lowest *P* value has been reached. Fourth, in a SCED study, 1 outcome is repeatedly measured in the same person. These replicated single-case experiments may be considered as multiple studies that can be combined using meta-analytical procedures [61,62]. To evaluate the overall changes in the daily diaries the daily data in phase A, phase B, and follow-up a multilevel analysis will be used to summarize the single-case data. Previously calculated effect sizes will be combined.

Missing data will be handled according to the randomized-marker method, in which all days of the diary that were not completed will be displayed as “N/A” (not applicable) [63].

For the other primary outcome measurements (USER-P and EQ-5D-5L) and the secondary outcome measurements, the results on T0, T1, and T2 will be computed as total scores on each questionnaire individually. Outcomes will be presented in mean (SD) or median (IQR), depending on the distribution. Outliers will be checked, defined as values more than 3 times the IQR from the median. The statistical analysis of the questionnaires will use repeated measures ANOVA in case of normal distribution or the Friedman test in case of nonnormal distribution. The statistical analysis of the physical examination will use the paired 2-tailed Student *t* test in case of normally distributed variables or the paired Wilcoxon test in case of nonnormally distributed variables. The significance level was set at *P*=.05, 95% CI. The statistical analysis will use IBM SPSS statistics version 26. No imputation will be made for missing data.

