## Methods

### Study Design

The design is R-SCED. This R-SCED study will use repeated measurements according to an AB follow-up design. In this design, patient functioning is closely monitored during a baseline phase (A), a treatment phase (B), and a follow-up phase. The length of phase A is 2 weeks. Phase B lasts for 12 weeks for all participants, and the follow-up phase lasts for 12 weeks. Figure 1 is a schematic presentation of the design, with treatment design and measurements (T0: beginning of phase A; T1: after completion of phase B; and T2: after completion of the follow-up phase). This R-SCED will be performed at Adelante Zorggroep, location MUMC+, which is an outpatient rehabilitation center in the south of the Netherlands.

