### Baseline Phase (Phase A)

The baseline phase (phase A) is the control period of each participant. No specific treatment will be given during this period. The start of phase A is determined based on the start date of the interdisciplinary rehabilitation treatment and lasts 2 weeks. The number of days (7, 8, 9, or 10) a participant must fill in a daily diary during phase A will be randomized by a dedicated computer program (YourResearch). Phase B will start directly after phase A.

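### The analysis says the start of phase B is random, but the design sections randomize only the number of diary days, so the diary randomization test has no design-based guarantee of its error rate as described

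*Protocol article*

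**What the plan says.** Two parts of the protocol article describe the start of treatment differently.

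- Statistical Analysis, third step: "Because the starting point of phase B (intervention) is randomly determined". The clause is given as a reason for combining phase B with follow-up. It sits inside the description of the randomization test, whose statistic is "mean phase A – mean phase BC = test statistic".
- Study Design: "The length of phase A is 2 weeks". No set of possible lengths is given.
- Baseline Phase (Phase A): "The start of phase A is determined based on the start date of the interdisciplinary rehabilitation treatment and lasts 2 weeks". The same section says "The number of days (7, 8, 9, or 10) a participant must fill in a daily diary during phase A will be randomized" and "Phase B will start directly after phase A".
- Follow-Up Phase: again only the number of diary days is drawn; the days that "a participant must fill in a daily diary during the last 2 weeks of the follow-up phase, will be randomized".

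No section describes a random draw of the day on which treatment begins.

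**The concern.** A start-point randomization test compares the observed boundary between baseline and treatment with the other boundaries that the draw could have produced. Its error rate is guaranteed because treatment could really have begun at each of them. If the treatment date comes first and baseline is counted back from it, each participant had one possible start. The alternative splits would then move treatment days into baseline, or the reverse, and the described draw could not have produced those assignments.

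The diaries are a primary outcome and this is their formal hypothesis test. Randomization is also part of the design's name. What is at stake is whether the diary P values can be presented as protected by randomization, or only as valid under an assumption about how the series behaves around the start date.

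**Working it through.** **Step 1: follow the stated timeline.**

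1. Phase A lasts 14 days for everyone (Study Design; Baseline Phase).
2. Its start is set from the treatment start date (Baseline Phase).
3. Phase B follows directly (Baseline Phase).
4. So the start of phase B equals the start of phase A plus 14 days, which is the date that was given at the outset. The draw of 7–10 does not enter.
5. The draw fixes how many of the 14 days carry a diary, leaving 14 − 10 = 4 to 14 − 7 = 7 days without one. The article does not say where those empty days fall.

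The position of phase B in the sequence of diary entries is therefore random, but its position in time is not. The statement in Statistical Analysis concerns the latter.

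**Step 2: what a real draw would give.** With four equally likely starts the smallest possible P is 1/4 = 0.25 for one participant, (1/4)² = 0.0625 for two and (1/4)³ ≈ 0.016 for three. The check below therefore uses a test pooled over 20 participants. Pooling is an assumption, because the article does not set out how the participants' randomization tests are combined.

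**Step 3: does the error rate suffer?** There is no figure in the plan to reproduce, so this is a simulation.

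- From the article: 20 participants; 7–10 baseline diaries; "there are 40 measurements during the rehabilitation treatment"; 7–10 follow-up diaries; 5% level.
- Assumed: lag-1 autocorrelation 0.3, unit SD, baseline diaries on consecutive days up to the start, candidate boundaries after entry 7, 8, 9 or 10, and no treatment effect.
- The statistic was signed so that improvement is positive. The article does not state sidedness, so both are shown where available.
- Runs used between 600 and 1500 trials. At 1000 trials the standard error at a true 5% is √(0.05 × 0.95 / 1000) ≈ 0.7 percentage points. Ranges cover repeat runs.

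| Pattern with no treatment effect | Start fixed, one-sided | Start fixed, two-sided | Start truly follows the draw, one-sided |
|---|---|---|---|
| Flat series | 4–6% | 5–6% | 4–5% |
| Saturating drift | 4.3% | not run | 5.1% |
| 0.5 SD shift exactly at the start date | 40.2% | not run | 4.5% |
| All start on Monday, weekends 0.5 SD lower | 37–41% | 26–29% | 4–6% |
| All start on Monday, weekends 0.3 SD lower | 18–22% | about 12–13% | 4–5% |
| All start on Monday, weekends 0.3–0.5 SD higher | below 1% | 13–28% | 3–5% |
| Start varies Monday–Friday, weekends 0.5 SD lower | 6–10% | 4–6% | – |
| Start varies Monday–Friday, weekends 0.3 SD lower | 5–7% | 5–6% | – |

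When the start truly follows the draw, the level holds in every pattern tried. When it is fixed, the level depends on the pattern. It survives a flat series and a smooth drift, stays near 5% in most cells with varied weekdays, and fails when something else changes in step with the start date for everyone.

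**The case against.** Several points on the other side stand.

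- **The article is condensed.** The design figure and the full protocol are not shown. The start may in fact have been drawn at random, in which case the 2-week statements are what is wrong. A reader might infer that treatment starts were certainly not randomized; the documents do not show that. They show only that the published sections cannot all be right. This is a conflict between positive statements, not an omission, so condensation does not excuse it.
- **The sentence is offered as a reason for pooling phase B with follow-up**, not as a validity argument for the test. That is so. It still states a random start as fact, within the randomization-test step, and it is the only such basis the article gives.
- **The large error rates rest on an assumed schedule.** Nothing in the article says that everyone starts on the same weekday, that diaries run over weekends, or that weekend scores differ. Ten diary days in two weeks would also fit weekday-only diaries, and a run on that basis gave 5–6%. A reader might infer that the test's error rate is 20–40%; the documents do not support that.
- **A reader might infer that the test is valid only if the series is stationary.** That is too strong, since a non-stationary saturating drift left the level at 4.3%.

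The defence that 7–10 entries make the position of phase B random does not stand. It makes the entry number random, not the day of treatment.

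**Conclusion.** The point holds as a contradiction with a limited consequence. Study Design and Baseline Phase describe a treatment start that is not drawn, while Statistical Analysis says it is. As described, the randomization test on the primary diary outcome loses the guarantee that randomization would give. That does not make the test invalid. Its level was about 4–6% for a flat series or a smooth drift and near 5% in most settings with varied start weekdays (up to about 10% one-sided with a 0.5 SD weekend dip). It ranged from about 12% to 41% if all participants started on a Monday with a 0.3–0.5 SD weekend dip. With a weekend rise, a one-sided test for improvement fell below 1%. The weekday and weekend inputs, the autocorrelation of 0.3, consecutive baseline diaries and the pooled form of the test are all assumptions.

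The visual analysis, Nonoverlap of All Pairs, and the USER-P and EQ-5D-5L questionnaire analyses do not depend on the draw and are not affected by this point.

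**What to change.** Before analysis, reconcile Study Design, Baseline Phase and Statistical Analysis by establishing what was randomized. Because diaries may simply have run up to the start, the gap between first diary and first treatment day can equal the drawn number under either reading. The telling question is whether each first treatment day was fixed before the draw or followed from it.

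- **If the first treatment day followed the draw:** correct the fixed 2-week phase A in Study Design and Baseline Phase, and state the set of possible start days as the test's reference set.
- **If it did not:** delete the random-start clause from Statistical Analysis. Report the test as a permutation analysis whose P value rests on exchangeability of the series around the start date, and drop the claim of design-based randomized inference. A multilevel model adjusted for day of week is an optional sensitivity analysis. It need not replace the planned test, and it would not remove other changes that coincide with the start.

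The cost is a check of records and a few sentences. In the second case the diary P values also carry a weaker causal claim.

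### The randomization test on the primary diary outcome is repeated over lags until the lowest P value is found, so that P value is not valid; how far the error rate rises depends on details the plan leaves open

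*Protocol article*

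**What the plan says.** The Statistical Analysis section applies four steps to the diaries, which it introduces with "For our primary outcome measurements, the daily dairies": visual analysis, Nonoverlap of All Pairs, randomization tests, and a multilevel summary. The third step carries the hypothesis test. Its null is "that the interdisciplinary rehabilitation treatment has no effect on participation levels and HRQoL", and its statistic is the mean of phase A minus the mean of phase B and follow-up combined.

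The lag rule follows, and it is triggered by the plots: "In case visual analysis suggests delayed effects, the randomization test will be repeated with lagged data until the lowest" *P* value is found.

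The section does not say what lagging does to the early phase B days, how many lags may be tried, or whether lagged runs are only supportive. One level appears, "The significance level was set at *P*=.05, 95% CI", at the end of the paragraph on the questionnaires and physical tests. None is given separately for the diary test.

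The Treatment Phase (Phase B) section says that "the first 4 weeks consist of an assessment phase", followed by an 8-week tailored plan.

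**The concern.** A randomization test is valid because its statistic is fixed before the outcomes are seen and is compared with the distribution of that same statistic over all possible assignments. Here the outcomes enter twice: the plots decide whether lags are tried, and the P values decide which lag ends the search. Each P value is correct for its own lag, but the smallest of them is not, because the comparison distribution takes no account of the choice.

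This is a rule the article states, not a detail left to a fuller document. It governs the only stated test of the no-effect null on the diaries. If the lowest P value is used as evidence, a claim of effect could rest on the search alone.

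**Working it through.** **Inputs from the article**
- 20 participants (Sample Size Calculation).
- 7, 8, 9 or 10 baseline diary days, drawn at random (Baseline Phase), so 4 possible start points. The number drawn is taken as the random start of phase B, as the Statistical Analysis section treats it.
- 40 diary days in phase B (Treatment Phase) and 7 to 10 in follow-up (Follow-Up Phase; Assessment).
- Statistic: mean A minus mean BC.

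**Assumptions, because the article does not state them**
- The statistic is averaged over the 20 participants and P is judged at .05.
- The series is fixed at 57 days (8.5 + 40 + 8.5).
- Lag-1 autocorrelation is 0 or 0.3.
- The search is made in every trial.
- Lagging by l days after start s means one of two things. *Moved*: A is days 1 to s + l and BC is the rest. *Dropped*: A is days 1 to s and BC starts after day s + l.

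**Single participant.** With 4 equally likely starts, the smallest possible P at any one lag is 1/4 = 0.25. No individual test can reach .05, so an error rate at that level arises only when participants are pooled.

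**Procedure.** 2,000 trials with no effect and 499 re-randomizations each. For each lag, P(l) is the share of assignments with a statistic at least as extreme as the observed one. The searched result is min P(l) over l = 0 to L, and the null is rejected if this is at most .05.

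**Reproducing the nominal level first.** At lag 0 the eight estimates run from 0.042 to 0.062 and average 0.051. The Monte Carlo standard error is √(0.05 × 0.95 / 2000) = 0.005. The unsearched test holds its level.

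**Searching for the lowest P** (one-sided / two-sided; the last row is one-sided)

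| Lags searched | Moved, AR 0 | Moved, AR 0.3 | Dropped, AR 0 | Dropped, AR 0.3 |
|---|---|---|---|---|
| 0 only | 0.050 / 0.056 | 0.062 / 0.053 | 0.048 / 0.048 | 0.046 / 0.042 |
| 0-3 | 0.184 / 0.195 | 0.173 / 0.170 | 0.066 / 0.066 | 0.056 / 0.057 |
| 0-7 | 0.324 / 0.341 | 0.294 / 0.296 | 0.080 / 0.080 | 0.068 / 0.067 |
| 0-14 | 0.494 / 0.509 | 0.471 / 0.478 | 0.097 / 0.098 | 0.082 / 0.082 |
| Stop when P no longer falls | 0.144 | 0.153 | 0.058 | 0.054 |

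Further null runs agree. With days moved, 600 trials gave 13-18% (lags 0-3), 26-32% (0-7) and 41-46% (0-13), and 12-15% under the stop rule. With days dropped they gave about 7%, 8% and 10%, and about 6% under the stop rule. A run of 1,500 trials with days moved gave 16-19%, 28-33% and 43-50%.

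**Benchmark.** For k independent tests the error is 1 − 0.95^k: 0.185 for k = 4, 0.337 for k = 8 and 0.537 for k = 15. The moved reading behaves almost like independent tests. The dropped reading gives highly correlated ones.

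**Check of the remedy.** When the minimum P over lags 0-3 to 0-14 is referred to its own re-randomization distribution, the simulated error is 0.028 to 0.052, at or below about 5%.

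**The case against.** The strongest reply is that the large figures depend on choices the article does not make. Several parts of it stand.

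- *Meaning of lagged.* If early phase B days are dropped, the inflation is modest. The 13-50% figures belong only to the reading that moves them into phase A.
- *Stopping.* The rule can be read as stepping forward until P stops falling, which gives about 12-15% (moved) or 6% (dropped).
- *Trigger.* The search happens only when the plots suggest delay, so for each lag set these are the rates when the search is always made. The trigger uses the same outcomes, however, and does not restore 5%.
- *Pooling.* Participants are combined in the fourth step through effect sizes; no pooled randomization P is described. The method matters. Combining each participant's lowest P by Edgington's method gave 0.58-0.81 for lags 0-3 with days moved, but at most 0.01 with days dropped, because P values from 4 starts are so coarse.

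A reader might infer that the lowest P replaces the unlagged one and is judged at .05. The article says neither: the unlagged test is run first and remains available to report, and the .05 level stands in another paragraph.

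A reader might also infer that the 4-week assessment period makes any search for a lag needless. It makes delay foreseeable, but treatment is individually tailored, so the delay may differ between participants.

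What does not stand is any defence of the stopping criterion itself. Choosing a lag because it gives the smallest P has no inferential basis under either reading.

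**Conclusion.** The rule is wrong as written and should be changed before the diaries are analysed. The lowest P value over an open-ended, data-triggered set of lags is not a valid P value.

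The size is uncertain. For a test pooled over 20 participants at .05 with the search always made, 5% becomes roughly 6-10% with days dropped. With days moved it becomes roughly 13-20% (lags 0-3), 26-34% (0-7) or 40-50% (0-13 or 0-14), or 12-15% with early stopping.

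It would go too far to conclude that the trial would often declare an ineffective treatment effective, or that its whole primary analysis has lost error control. The first holds only under some readings of undefined terms. The second fails because the multilevel summary and the USER-P and EQ-5D-5L analyses do not use the lag rule.

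**What to change.** In the Statistical Analysis section:
1. Delete the clause that makes the lowest P value the stopping point.
2. Define lagged data: state whether early phase B days are dropped or counted with phase A.
3. Name the unlagged test, or one lag fixed before the data are viewed, as the primary randomization test, and report it whatever it shows. The 4-week assessment period is one design-based way to choose such a lag.
4. Label every other lag exploratory.

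If several lags are wanted in the primary test, fix the set in advance, take the maximum statistic or minimum P over it, and compare that with its own re-randomization distribution over the same set.

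The change takes a few sentences and no new data. It may give a less favourable P value, and power is lost if the fixed lag does not match the true delay, which may vary between participants. The fixed-set version avoids relying on one lag and keeps the error at about 5%.
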